#### Self-Management Behavioral Strategies

Participants receive modular evidence- and theory-based smartphone push notifications that are designed to facilitate uptake and maintenance of chronic disease self-management behaviors. Behavioral content includes information (ie, education) and strategies (ie, behavior change techniques) to support heart health, physical activity and sedentary behavior, healthy eating and alcohol consumption, stress management, and—when indicated—smoking cessation (Table 1). Educational and behavioral content progresses over the intervention period to promote uptake, short-term adherence, relapse prevention/reuptake, and long-term self-determined maintenance. Participants are encouraged to activate all modules to facilitate multifactorial behavioral support, but they can activate/deactivate individual modules via the SCRAM app to meet their individual needs and preferences. Notification frequency depends on the number of active modules (Table 1). Activation (or reactivation) of modules after the start of the intervention period triggers a single-batch receipt of content that was scheduled for delivery before the (re)activation date. For example, if a module is activated 2 weeks after starting the intervention, all messages scheduled for receipt during the first 2 weeks are delivered in a single batch. Subsequent messages are received as per the normal delivery schedule. This approach maximizes behavioral support and preserves the progressive nature of education and behavior content over the intervention period, while also enabling participants to tailor the types of support they receive to meet their individual needs.

**Table 1 table1:** Outline of self-management behavioral support modules.

Notification content			Weekly frequency (n)		
Module	Topics		Intensive phase		Maintenance phase
Heart health	Information about CHD^a^ risk factors, medication beliefs, illness perceptions, and medical checkups; behavioral strategies to facilitate uptake and maintenance.	4		3	
Physical activity and sedentary behavior	Information about the physical activity, sedentary behavior; activity suggestions; behavioral strategies to facilitate uptake and maintenance.	2		1	
Healthy eating	Dietary recommendations for vegetables, fruit, wholegrains, legumes, fat, salt, and alcohol; emphases on variety, recipes, meal planning and preparation methods, cooking techniques, and mindfulness; behavioral strategies to facilitate uptake and maintenance.	2		1	
Stress management	Information about emotional strain and negative affect, as well as strategies to facilitate uptake and maintenance of stress management behaviors.	2		1	
Smoking cessation (if indicated)	Information about the impact of tobacco smoking on health and sources of smoking cessation support, as well as strategies to facilitate the reduction and cessation of tobacco smoking.	2		1	

^a^CHD: coronary heart disease.

### Maintenance Phase (Weeks 13-24)

#### Exercise Training

Participants continue to receive individualized and progressive exercise prescription during the maintenance phase; however, the format of supervision and coaching changes. Participants quantify their exercise performance using the SCRAM smartphone app and wearable sensor as per the intensive phase, but they no longer receive real-time supervision or coaching throughout training sessions. Instead, exercise physiologists provide individualized coaching feedback and update exercise prescription parameters during weekly telephone calls, based on assessment of participants’ exercise performance and goal achievement using retrospective review features of the Web app. Nonadherence (ie, absence of recorded data) initiates prompts from exercise physiologists to promote reengagement.

As per the intensive phase, participants use the smartphone app to self-monitor exercise performance (in real time during exercise and retrospectively afterward using automated graphing elements); set exercise goals and review goal achievement feedback (using automated graphing elements); and receive evidence- and theory-based behavioral support push notifications.

### Self-Management Behavioral Support

Self-management behavioral support—as described above—is delivered at a reduced frequency during the maintenance phase; notification frequency depends on the number of active modules (Table 1). Content emphasizes behavioral strategies that promote long-term adherence, including autonomy, self-directed motivation, and relapse prevention.

#### Theoretical Framework

Features and content of the SCRAM intervention are informed by Social Cognitive Theory, Self-Determination Theory, the Common Sense Model, and the Taxonomy of Behavior Change Techniques [31-34]. Theory-based platform components are designed to enhance task and barrier self-efficacy; perceptions of competence, autonomy, and relatedness; and perceptions of control over health and well-being, as these constructs influence the uptake and adherence of self-management behaviors [35-38].

Real-time biofeedback and exercise coaching during the intensive phase have been designed to support task self-efficacy and perceived competence by providing information about participants’ exercise performance and progress toward prescribed exercise targets (ie, reinforcing mastery experiences via verbal persuasion). Delivery of exercise coaching by real accredited exercise physiologists—rather than automated processes—was chosen to enhance participants’ perceived relatedness by providing a sense of connection and social support.

The remote intervention delivery model has been designed to support participants’ perceived autonomy by enabling them to choose preferred aerobic exercise modes, exercise locations/routes, and exercise times (within predefined operating hours during the intensive phase). Enabling participants to develop exercise task and barrier self-efficacy in their own environment may also support long-term behavior change by overcoming barriers associated with transitioning away from the specialized facilities and equipment provided in center-based settings.

The smartphone app dashboard has been designed to support perceived competence and task self-efficacy by enabling participants to set individualized exercise goals, view automated goal achievement feedback, and self-monitor their exercise performance and progression throughout the intervention. Self-monitoring features provide access to brief summary data, as well as full-resolution data, to cater to varying participant engagement and preferences.

Behavioral support content builds on our previous CR SMS interventions that have been shown to improve self-management behaviors [10,39,40]; the larger character allowance of push notifications has been used to integrate more natural language than is typically possible with a 160-character SMS.

Table 2 summarizes the integration of 24 separate behavior change techniques into the exercise training and behavior change support components of the SCRAM intervention. Two techniques are implicit in the dual-phase design (7.3 Reduce prompts/cues) and inclusion of accredited exercise physiologists for exercise program delivery, as well as behavioral scientists for push notification content creation (9.1 Credible source). The remaining 22 techniques are collectively used 622 times across all push notification modules. Instances of behavior change techniques cannot be prospectively quantified for the exercise monitoring/coaching and goal setting/self-monitoring intervention components, as they are dependent on exercise physiologist interactions and participants’ app usage, respectively.

**Table 2 table2:** Integration of behavior change techniques into *Smartphone Cardiac Rehabilitation, Assisted self-Management* exercise training and behavioral support intervention components.

Behavior change technique	Exercise training		Push notification modules (n)					
	Monitoring+coaching	Goals+self-monitoring	Heart health	Physical activity	Healthy eating	Stress management	Smoking cessation	Total
1.1 Goal setting (behavior)	Yes	Yes	22	9	12	10	6	59
1.2 Problem solving	N/A^a^	N/A	17	18	6	3	10	54
1.4 Action planning	N/A	N/A	31	12	17	15	15	90
1.5 Review behavior goal(s)	Yes	Yes	6	4	0	N/A	4	14
1.6 Discrepancy between current behavior and goal	Yes	Yes	10	5	2	N/A	N/A	17
2.3 Self-monitoring of behavior	Yes	Yes	42	19	24	20	15	120
3.1 Social support (unspecified)	Yes	N/A	7	0	1	2	0	10
3.3 Social support (emotional)	Yes	N/A	15	9	1	9	8	42
4.1 Instruction on how to perform behavior	Yes	N/A	17	16	14	12	3	62
5.1 Information about health consequences	N/A	N/A	9	4	12	9	10	44
7.1 Prompts/cues	N/A	N/A	3	0	0	0	2	5
7.3 Reduce prompts/cues	Yes^c^	N/A	Yes^b^	Yes^b^	Yes^b^	Yes^b^	Yes^b^	Yes^b^
8.2 Behavior substitution	N/A	N/A	2	2	8	0	0	12
8.3 Habit formation	N/A	N/A	3	2	0	0	0	5
8.4 Habit reversal	N/A	N/A	0	1	0	0	1	2
8.7 Graded tasks	Yes	N/A	5	4	3	0	3	15
9.1 Credible source	Yes^c^	N/A	Yes^c^	Yes^c^	Yes^c^	Yes^c^	Yes^c^	Yes^c^
10.4 Social reward	Yes	N/A	16	13	5	2	5	41
10.9 Self-reward	N/A	N/A	2	0	0	0	0	2
11.1 Pharmacological support	N/A	N/A	1	0	0	0	3	4
12.1 Restructuring the physical environment	N/A	N/A	2	0	0	0	1	3
12.3 Avoidance/reducing exposure to cues for the behavior	N/A	N/A	0	0	0	0	3	3
15.1 Verbal persuasion about capability	Yes	N/A	5	1	1	2	3	12
15.3 Focus on past success	Yes	Yes	11	0	1	2	0	14
Number of discrete behavior change technique within intervention components	11	5	20	15	14	11	16	24
Total instances of behavior change technique use within intervention components	—^d^	—^d^	226	119	107	86	92	630

^a^Not applicable.

^b^Implicit in the dual-phase intervention design.

^c^Implicit in inclusion of accredited exercise physiologists and behavioral scientists in intervention design and delivery.

^d^Instances of behavior change technique use cannot be prospectively quantified for these features.

#### Outcomes

Outcome measures and the assessment schedule are summarized in Table 3. 

Baseline and 24-week assessments are conducted at trial centers; 12-week assessments are conducted via telephone and internet survey. Furthermore, 12- and 24-week assessments are permitted ±2 weeks of the scheduled date to meet participant scheduling commitments. Participants who do not attend assessments are rescheduled for a second appointment; those who do not complete the 12-week assessment but do not withdraw their participation are contacted to complete the 24-week assessment. If participants cannot attend the 24-week assessment in person, self-report data may be collected via telephone and internet survey to minimize missing data.

Demographic and eHealth literacy data are collected at baseline to describe sample characteristics. Clinical data (diagnosis and treatment, hospitalization, and medication) are obtained with consent from hospital records, where possible. Self-reported adverse events are recorded and/or updated throughout the participation period as required.

**Table 3 table3:** Schedule of enrollment, treatments, and assessments.

Activity		Description		Weeks −4 to 0		Week 0		Week 12		Week 24	
Enrollment		Contact details, eligibility criteria, verbal consent for trial referral		Yes		N/A^a^		N/A		N/A	
Consent		Trial procedures, health care/medication utilization data release		N/A		Yes		N/A		N/A	
Allocation		Concealed centralized computer-based randomization		N/A		Yes		N/A		N/A	
**Treatments**											
	Control		Usual cardiac rehabilitation care alone		N/A		Start		Ongoing		Finish
	Intervention		*Smartphone Cardiac Rehabilitation, Assisted self-Management*		N/A		Start intensive phase		Start maintenance phase		Finish
**Characteristics**											
	Sociodemographic		Age, sex, ethnicity, income, education, and occupation		N/A		Yes		N/A		N/A
	Clinical		Diagnostic, smoking and alcohol history, and medication		N/A		Yes		N/A		N/A
	Electronic health literacy		Electronic Health Literacy Questionnaire [41]		N/A		Yes		N/A		N/A
**Primary outcome**											
	VO_2_max^b^		Maximal treadmill cardiopulmonary exercise test		N/A		Yes		N/A		Yes
**Secondary outcomes**											
	Anthropometry		Body mass, body mass index, and waist and hip circumferences		N/A		Yes		N/A		Yes
	Blood lipid concentrations^c,d^		Total/high-density lipoprotein/low-density lipoprotein cholesterol, and triglyceride		N/A		Yes		N/A		Yes
	Blood glucose concentration^c,d^		≥3 hours fasted		N/A		Yes		N/A		Yes
	Blood pressure^c,d,e^		Automated sphygmomanometer		N/A		Yes		N/A		Yes
	Physical activity		Godin Leisure Time Physical Activity Questionnaire, % reporting leisure score index ≥ 14 units [42]		N/A		Yes		Yes		Yes
	Dietary intake		Automated self-administered 24-hour dietary assessment tool-Australia, dietary guideline index, and vegetable and discretionary food consumption [43-46]		N/A		Yes		Yes		Yes
	Alcohol consumption		3-item Alcohol Use Disorders Identification Test-C Questionnaire, % reporting ≤2 drinks/day [47]		N/A		Yes		Yes		Yes
	Medication adherence		4-item Medication Adherence Scale, % adherent (score=4) [48]		N/A		Yes		Yes		Yes
	Health-related quality of life		Assessment of Quality of Life 8-dimension, multiattribute utility score [49]		N/A		Yes		Yes		Yes
	Adverse events^f^		Self-reported changes to health status		N/A		Yes		Yes		Yes
Economic evaluation		Delivery, health care/medication use, and participant costs		N/A		N/A		N/A		Yes	
Process evaluation		Semistructured interviews; utilization data		N/A		N/A		N/A		Yes	

^a^Not applicable.

^b^VO_2_max: maximal aerobic exercise capacity.

^c^Measured after ≥3 hour fast.

^d^Measured before cardiopulmonary exercise test.

^e^Measured after ≥10 min of seated rest.

^f^Documented as required throughout the participation period.

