### Objectives

This protocol describes the rationale and design of a multicenter RCT that aims to compare the effects and costs of SCRAM on modifiable cardiovascular risk factors with usual care CR among urban-, regional-, and rural-dwelling individuals with CHD. Usual care CR was chosen as the comparator as it is the standard of care. We hypothesize that the effects of SCRAM on primary and secondary outcomes will be superior to usual care CR alone and that SCRAM will be cost-effective.

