#### Statistical Analysis

Baseline characteristics will be summarized descriptively for the full sample and by treatment group. A linear regression model—adjusted for baseline values and stratification variables—will be fitted to assess the primary outcome. Primary analyses will be performed on the principle of intention to treat. Assuming there is a reasonable amount (>5%) of missing data, primary analyses will be conducted using multiple imputation, imputing all outcomes using a single (joint) imputation model. Imputation models will include participant age, sex, type of diagnosis (eg, angina, myocardial infarction, and coronary revascularization), in addition to any other covariates that appear to predict missingness. A per-protocol analysis will be conducted with complete cases to test the robustness of treatment effects under different assumptions. Preplanned subgroup analyses will be conducted to determine treatment effects by levels of treatment adherence, sex, and trial center (Figure 1). Secondary analyses will adjust the regression model for baseline prognostic factors, including age, sex, and employment status.

A similar approach will be used to assess continuous secondary outcomes (Table 3); logistic regression will be used for binary outcomes. Model-adjusted estimates and group differences will be reported with 95% CIs and probability values. All statistical tests will be 2-sided at α=.05. The biostatistician will remain blinded throughout the analysis of treatment effects. A detailed statistical analysis plan will be developed before the completion of data collection to guide analyses.

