#### Sample Size

Our previous noninferiority trial [10] indicates that 174 participants are required to detect a clinically meaningful between-group difference of 2.0 mL**·**kg^−1^**·**min^−1^ in VO_2_max (SD 6.75 mL**·**kg^−1^**·**min^−1^, r=0.80 between repeated measures, β=.9, and 2-sided α=.05). Allowing for 20% loss to follow-up (17% in our previous trial), a total of 220 participants are required to ensure equal numbers per treatment arm (ie, 110 per arm). Minimum detectable between-group differences in secondary outcomes at 24-week follow-up are summarized in Table 4.

**Table 4 table4:** Minimum detectable differences in secondary outcomes (assuming a total sample size of 220 participants [110 per treatment arm] and beta=.8).

Secondary outcome	Group difference	Data source
Total cholesterol concentration	0.24 mmol·L^−1^	Maddison et al [10]
Low-density lipoprotein cholesterol concentration	0.16 mmol·L^−1^	Maddison et al [10]
High-density lipoprotein cholesterol concentration	0.10 mmol·L^−1^	Maddison et al [10]
Triglyceride concentration	0.29 mmol·L^−1^	Maddison et al [10]
Glucose concentration	0.60 mmol·L^−1^	Maddison et al [10]
Physical activity leisure score index	17%	Dale et al [40]
Health-related quality of life	0.06 units	Richardson et al [56]
Medication adherence	19%	Thornley et al [57]
Systolic blood pressure	4.70 mmHg	Maddison et al [10]
Diastolic blood pressure	2.76 mmHg	Maddison et al [10]
Body mass	3.80 kg	Maddison et al [10]
Body mass Index	0.90 kg/m^2^	Maddison et al [10]
Waist circumference	2.60 cm	Maddison et al [10]
Hip circumference	1.80 cm	Maddison et al [10]
Alcohol consumption	21%	Dale et al [40]
Dietary guideline index	3.70 units	Livingstone and McNaughton [45]

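### Physical activity is analysed only as the percentage past one cut-point, which costs about 20 to 30 percentage points of power that the collected score could keep

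*Protocol article*

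**What the plan says.** Three places in the protocol article agree on the form of this outcome.

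- **Table 3, secondary outcomes:** physical activity is "Godin Leisure Time Physical Activity Questionnaire, % reporting leisure score index ≥ 14 units", assessed at baseline, 12 weeks and 24 weeks.
- **Statistical Analysis:** "logistic regression will be used for binary outcomes". Continuous secondary outcomes get a linear model like that for the primary outcome. The same section states: "All statistical tests will be 2-sided at α=.05".
- **Sample Size, Table 4:** the row "Physical activity leisure score index" gives a detectable difference of 17%, "assuming a total sample size of 220 participants [110 per treatment arm] and beta=.8". The last figure is evidently power.

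The Objectives section expects benefit here: "We hypothesize that the effects of SCRAM on primary and secondary outcomes will be superior to usual care CR alone". Table 4 sizes the dietary guideline index and health-related quality of life in score units, and no reason is given for treating the leisure score index differently. The article says that a detailed analysis plan will be written before data collection ends; it is not shown.

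**The concern.** SCRAM is built around exercise training. Its intensive phase works up to 3 to 5 supervised or self-monitored sessions a week, so self-reported activity is the behavioural outcome closest to what the intervention does. Cutting the score at 14 units removes two kinds of change from the comparison: a rise in someone already above the cut, and a rise that leaves someone still below it. If activity shifts across the whole distribution, the binary comparison has clearly less power than the data allow. A real effect on a hypothesised outcome could then be missed although the information was collected.

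**Working it through.** **1. The plan's own figures.**

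Primary sample size, with difference 2.0, SD 6.75, r = 0.80, power 0.90 and two-sided α 0.05:
n per arm = 2 × (1.960 + 1.282)² × 6.75² × (1 − 0.80²) / 2.0² = 86.2, so 87 per arm and 174 in total. 174 / 0.80 = 217.5, so 218, stated as 220. This reproduces.

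Table 4 gives no control rate for physical activity, so its 17 points can only be checked for feasibility. Using the pooled two-proportion formula at 110 per arm and 80% power, the detectable difference is:

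| Control rate | 10% | 20% | 30% | 40% | 50% | 60% | 70% |
|---|---|---|---|---|---|---|---|
| Points | 14.1 | 17.0 | 18.3 | 18.8 | 18.5 | 17.4 | 15.6 |

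Seventeen points is attainable at a control rate near 20%, or between 60 and 70%.

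**2. Information kept by a cut.** For a normal score with proportion p past the cut, the fraction kept is φ(z)² / [p(1 − p)], with z the normal quantile of p.
- p = 0.5: 0.637
- p = 0.7: 0.576
- p = 0.8: 0.490

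**3. Same shift, two analyses, no baseline adjustment.** At 110 per arm the uncut score has 80% power for (1.960 + 0.842) × √(2/110) = 0.378 SD. After the cut, that shift has 57 to 60% power for control rates of 30 to 60%, 52% at 70% and 44% at 80%.

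Taking Table 4's 17 points as the truth (a shift of 0.43 to 0.485 SD at control rates of 30 to 60%):

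| Per arm | Cut | Uncut |
|---|---|---|
| 110 | 72 to 78% | 89 to 95% |
| 88 (220 less 20%, halved) | 62 to 68% | 81 to 90% |

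**4. With baseline adjustment.** Assumed: 88 per arm, a uniform shift of 0.4 SD, baseline correlation r of 0.4 to 0.6, and 40 to 60% of controls past the cut.

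For the normal score, power = Φ( 0.4 / [√(2/88) × √(1 − r²)] − 1.960 ):
- r = 0.4: 0.4 / (0.1508 × 0.9165) − 1.960 = 0.934, power 82%
- r = 0.6: 0.4 / (0.1508 × 0.8) − 1.960 = 1.357, power 91%

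For the threshold without adjustment, at a control rate of 50%: the intervention rate is Φ(0.4) = 65.5%, a difference of 15.5 points, and power is 55%. Adjusting for baseline in the logistic model raises this somewhat. Simulation of the adjusted analyses over the stated ranges gives:

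| Analysis | Power |
|---|---|
| Threshold, logistic | about 57 to 65% |
| Score, normal, linear | about 82 to 91% |
| Score, rank-based | about 80 to 89% |
| Score lognormal (log-SD 1), raw linear with robust errors | about 59 to 69% |

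The last row shows that the gain depends on the model: raw-score linear regression on a strongly skewed score is little better than the cut. If the score is lognormal, analysing its logarithm recovers the normal-score row.

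**5. Medication adherence, for comparison.** Assume five levels, with 40 to 70% scoring 4. Under proportional odds, the ordinal information is proportional to (1 − Σp³)/3 and the binary information to p(1 − p). The ratio is 0.79 to 0.97, so the cut loses about 3 to 21%.

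**The case against.** The strongest defence is that nothing here is wrong or contradictory. Tables 3 and 4 and the Statistical Analysis section agree on the binary form, the detectable difference is disclosed, the outcome is secondary, and a percentage past a threshold is clinically readable. All of that stands: this is an inefficient choice, not an error.

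The gain also rests on assumptions. The documents give no score distribution, control rate, correlation or expected shift. A uniform shift favours the score. If SCRAM mainly moves inactive people across the cut, the advantage shrinks and could reverse. The analysis plan may also add a supportive score analysis. That would help, but the article already fixes the percentage as the outcome.

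A reader might infer four stronger things, which the documents do not support.

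- **That all three thresholded behaviours lose much of their power.** Medication adherence is a 4-item scale cut at its top score and keeps most of its information. Alcohol is "3-item Alcohol Use Disorders Identification Test-C Questionnaire, % reporting ≤2 drinks/day", a consumption threshold and not a stated cut of the questionnaire total, so its loss cannot be quantified.
- **That the baseline covariate is reduced to yes or no.** The article only says that models adjust for baseline values. A logistic model can carry the uncut baseline score, and the choice moves power by only about 1 to 5 points.
- **That only very large effects are detectable.** A 0.4 SD shift is about 14 to 16 points at control rates of 40 to 60%, not far below the 17 in Table 4.
- **That a null result would be uninformative.** Estimates are reported with 95% CIs, which would still bound the effect.

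**Conclusion.** The point holds for physical activity. On the assumptions in step 4 of the working, the threshold analysis has about 57 to 65% power where a suitable baseline-adjusted score analysis has about 80 to 91%. The size is conditional on a roughly uniform shift and on a model that suits the score's shape. The primary outcome is unaffected. The change is worth making because it needs no new data and concerns the behaviour closest to the intervention. For medication adherence and alcohol, an ordinal analysis is at most an optional supportive one.

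**What to change.** - Before unblinding, prespecify a baseline-adjusted analysis of the leisure score index as the main physical activity analysis. Name the model now, with an ordinal, rank-based or transformed version if the score is skewed. Do not rely on raw-score linear regression in that case.
- Keep the percentage at or above 14 units, with its logistic model, as the clinical summary.
- Add the detectable difference in score units to the physical activity row of Table 4, and state the control rate behind the 17 points.

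Cost: one further model on data already collected. Score differences are less directly readable, which is why the percentage stays. The main analysis of a prespecified secondary outcome would change during recruitment (54 randomised by September 2019), so it must be documented as an amendment and the registration updated. The timing allows this: the article places the detailed analysis plan before the end of data collection and keeps the biostatistician blinded.
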